### Study design

2.2

The protocol was drafted using the SPIRIT guidelines and the results will be reported following the checklist of the Consolidated Standards of Reporting Trials statement (see Supplementary Table 1). All participants will be informed of the purpose of the study and obtain their informed consent before participating in this parallel group study. According to the inclusion and exclusion criteria, a total of 90 patients with functional constipation are expected to be recruited. Then they were randomly assigned to the Chinese medicine group (group A), placebo + diet group (group B), Chinese medicine + diet group (group C) at the ratio of 1: 1: 1. The patient filled out the case report form (CRF) after confirming enrollment, and the researchers recorded the patient's symptoms, bowel movements, etc., on day 14 (phone follow-up) and day 28. Interventions were provided to subjects based on the enrollment number, but neither the patient nor the investigator knew whether the patient was receiving drug or placebo. The entire study design is shown in the figure (see Fig. 1). A SPIRIT figure for the schedule of enrolment, interventions, and assessments is also presented (see Fig. 2).

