### Sample size

2.5

Because there is still insufficient clinical evidence, this study is a small sample exploratory study with a total sample size of 90 people (each treatment group has 30 samples).

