### Planned statistical analysis

2.14

Continuous variables will be described as the mean ± standard deviation, median, or interquartile range. The number of cases, frequency, the rate, and the constituent ratio will be described by categorical variables. Variance analysis will be used for continuous variables in the baseline data having normal distribution and same variance. Wilcoxon rank sum test or Kruskal–Wallis H test will be used for the comparison of differences between groups that are not normally distributed or have uneven variance. Categorical variables will be tested by *χ*^2^ test or Fisher exact test. Wilcoxon rank sum test or Kruskal–Wallis H test will be used for the number of CSBM per week in primary outcome. *χ*^2^ test or Fisher exact test will be used for percent improvement of each symptom scale score in secondary outcome indicators. The result of 48-hour GITT will be analyzed using *χ*^2^ or Fisher test. Wilcoxon rank sum test or Kruskal–Wallis H test will be used for measurement data in HRAM, while *χ*^2^ test or Fisher exact test will be used for counting data. Safety, dietary quality, compliance indicators will be tested by *χ*^2^ test or Fisher exact test. Complying with the intent-to-treat and per-protocol principle, all data of the patients randomized and at least 1 assessment (include baseline assessment) will be analyzed. For dropouts and terminations, their missing data will be obtained by last-observation-carried-forward method. All statistical analyses will be performed by SPSS23 software (IBM, Chicago, IL), and *P* value <.5 will be considered statistically significant.

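### The only significance threshold is printed as P < .5, very probably a slip for .05; as written, about half of true-null rank and chi-square tests would count as significant

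*Protocol article*

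**What the plan says.** Section 2.14 sets out the tests and closes with the decision rule. For weekly complete spontaneous bowel movements (CSBM), the primary outcome, "Wilcoxon rank sum test or Kruskal–Wallis H test will be used for the number of CSBM per week in primary outcome". For the symptom scales, the χ² "test or Fisher exact test will be used for percent improvement of each symptom scale score in secondary outcome indicators". Chi-square or Fisher is also named for 48-hour transit, for safety, and for diet quality and compliance.

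The last sentence begins "All statistical analyses will be performed by SPSS23 software" and ends with the threshold: a P "value <.5 will be considered statistically significant". Because the two parts share a sentence, the threshold applies to all the analyses.

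The document gives no other significance level. Section 2.5 (Sample size) says that "this study is a small sample exploratory study with a total sample size of 90 people (each treatment group has 30 samples", and states no alpha, power, effect size or standard deviation. Section 2.2 (Study design) allocates "at the ratio of 1: 1: 1" to three groups.

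**The concern.** The figure is ten times the conventional .05 and is the only criterion by which any result of the trial would be called significant. This is a figure stated wrongly, not a detail that an article leaves to a fuller document.

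The Discussion says the trial is meant to clarify the efficacy and safety of the diet and the herbal formula. Under the printed rule the word significant would carry almost no evidence on either. It would mark differences on the primary outcome, the secondary outcomes and safety at rates close to a coin toss when no difference exists.

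**Working it through.** There is no plan figure to reproduce: the threshold is a stated convention and the sample size has no statistical inputs. The check is what the printed rule does when there is no true difference.

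**Inputs from the document.** Threshold .5; three groups of 30; Wilcoxon or Kruskal–Wallis for the primary outcome; chi-square or Fisher for categorical outcomes.

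**Assumptions.** Two-sided tests (sidedness is not stated); weekly CSBM counts simulated as Poisson with mean 2, or as overdispersed gamma-Poisson counts; common event rates of 0.1, 0.3 and 0.5 for the categorical tests.

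**Step 1: critical values.** Two-sided z is Φ⁻¹(1 − α/2): 0.674 at .5, against 1.960 at .05. For a three-group Kruskal–Wallis test (chi-square, 2 degrees of freedom) the critical value is 1.39, against 5.99.

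**Step 2: single tests under the null, 30 per arm.** The rank tests were simulated (10,000 Poisson trials). The categorical tests, 30 against 30, were enumerated exactly, with no continuity correction for chi-square.

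| Test | P < .5 | P < .05 |
|---|---|---|
| Kruskal–Wallis, three groups | 50.1% | 4.5% |
| Wilcoxon, two groups | 50.0% | 4.6% |
| Chi-square | 48% to 52% | 4.9% to 5.4% |
| Fisher exact | 29% to 37% | 0.9% to 2.7% |

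Fisher's test falls below its nominal level because it is discrete and conservative. In 4,000 trials with gamma-Poisson counts, Kruskal–Wallis rejected in 50.4% at .5 and 5.5% at .05.

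**Step 3: three pairwise tests on the primary outcome.** If the comparisons were independent, the chance of at least one positive would be 1 − (1 − .5)³ = 87.5%, against 1 − (1 − .05)³ = 14.3%. They are not independent, because each arm enters two of them. The gamma-Poisson simulation gave 77.8% at .5 and 12.3% at .05; a further check gave 77% to 78% and about 11%.

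A large-sample approximation agrees. With equal arms, at least one pairwise |z| exceeds c when the range of three standard normal values exceeds c√2. At .5, c√2 = 0.674 × 1.414 = 0.954, and the probability is 77.8%. At .05, c√2 = 1.960 × 1.414 = 2.772, and the probability is 12.2%.

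**Step 4: secondary outcomes.** Section 2.11.3 lists 1 constipation symptom scale, 1 TCM syndrome scale, 3 transit parameters, 6 manometry parameters, the stool form scale, PAC-QOL, PAC-SYM and 7 short-chain fatty acids: 1 + 1 + 3 + 6 + 1 + 1 + 1 + 7 = 21. With one test each and no true differences, the expected number called significant is at most about 21 × .5 = 10.5, against 21 × .05 = 1.05. It is lower to the extent that Fisher's test is used.

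**The case against.** The strongest reply is that this is a dropped zero that nobody would follow. Section 2.13 gives the analysis to an independent statistician, who would probably notice. That makes the literal consequences less likely, but it does not correct the sentence, which is the only published criterion.

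A second reply is that an exploratory trial may choose a lenient level. There is a statistical trade-off here: for an assumed difference of 0.5 SD with 30 per arm, the expected z is 0.5 × √(30/2) = 1.936. Power is then about Φ(1.936 − 1.960) = 49% at .05 and Φ(1.936 − 0.674) = 90% at .5. But the sections that call the study exploratory (2.1, 2.3, 2.5) do not offer this as a reason for .5, and the document does not discuss the choice at all.

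Two stronger readings are tempting and should be resisted. A reader might infer that half of all null comparisons would be declared significant. That holds for the rank tests and approximately for chi-square, but not for Fisher's exact test, which section 2.14 allows for the categorical variables.

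A reader might also infer that the trial would almost certainly announce an effect of the herb or the diet. On the primary outcome alone the chance is about 50% with Kruskal–Wallis, or 78% for any of three pairwise tests. The 78% counts differences in either direction and includes herb alone against placebo plus diet, a contrast that isolates neither component. Near-certainty arises only if any of the many secondary variables also counts as a finding.

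**Conclusion.** The point stands as a wrong figure in the operative decision rule, very probably typographical. That the sentence needs correction is certain. The size of the effect depends on the rule being applied as printed.

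The 50% for the rank tests follows from the threshold itself and hardly depends on the assumed counts. The 29% to 37% for Fisher depends on the assumed event rates. The 78% depends on the three comparisons being made pairwise by Wilcoxon tests without adjustment, which the document permits but does not specify. The simulated values rest on assumed count distributions, although the large-sample approximation gives the same result. That .05 was intended, and that tests are two-sided, are conventional readings and are not stated in the document.

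**What to change.** Correct the last sentence of section 2.14 to the intended level and state its sidedness, conventionally: *a two-sided P value < .05 will be considered statistically significant*.

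The cost is one line. The sample size of 90 does not change, because section 2.5 did not derive it from an alpha. If the protocol approved by the ethics committee carries the same figure, the written application described in section 2.15 applies, and the correction should be made before unblinding.

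The correction does not settle which group contrasts are primary or how three pairwise comparisons would be handled; those are separate decisions and not part of this point.

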### Ethics and dissemination

2.15

This study has been approved by China-Japan Friendship Hospital clinical research ethics committee (No. 2017-46-1). Participants will need to sign the informed consent before the entering the study. During the intervention, patients have the right to withdraw at any condition and will not affect subsequent treatment (personal treatments from the expert team). We must submit a written application to the ethics committee if the protocol needs to be modified. The committee members will decide whether to modify it. The results of the study will be sent to researchers, participants, and disseminated to the public through academic conferences and journals. This is an open access article, which permits unrestricted use when the original work is correctly cited.

## Discussion

3

FC is a common disease of the digestive system and is characterized by persistent or recurrent difficulty in defecation. Constipation can cause digestive symptoms such as loss of appetite, abdominal distension, hemorrhoids, and colon polyps. It can also lead to cardiovascular and cerebrovascular diseases,^[18–20]^ kidney diseases,^[21,22]^ and even sudden death. At present, traditional Chinese and Western medicines used to treat functional constipation can only temporarily improve constipation. Constipation can easily recur after stopping the medication. Some traditional Chinese medicines also cause damage to the intestinal tract (melanosis coli).^[23,24]^ Long-term improvement of constipation can be achieved through the management of patients’ cognitive behavioral patterns. Studies have shown that dietary fiber supplementation can improve chronic constipation, but there is no intervention study on constipation with a vegan diet.^[25–27]^ In clinical practice, maintenance of FC improvement has been observed in patients who persist in LVD for a period of time without any drug use. TCM is a national medicine in China.^[28,29]^ It has been caring for the health of Chinese people from ancient times to present. TCM has mature experience in the treatment of constipation. Qing Jiang Tiao Chang Fang is a safe and effective prescription. However, these are only the results of clinical observations and need to be scientifically validated in clinical trials. This RCT aims to clarify the efficacy and safety of LVD and QJTCF on FC by designing rigorous trials. The results of the study can provide more evidence for dietary intervention and TCM intervention on FC, and to some extent, clarify the complementary effect of diet on drugs. There are still some limitations in this study:

1.Dietary intervention is a cognitive behavioral therapy, and there are many objective factors that will hinder the practice of light vegetarian diet and affect the experimental results.2.The experiment explored the metabolic effects of vegetarian diet and traditional Chinese medicine on fecal short-chain fatty acids, but no other metabolites were studied.3.The current study belongs to exploratory study with small sample size.

Therefore, based on this study, a large sample size, multicenter RCT should be designed in the future to verify the effectiveness and safety of LVD and QJTCF on FC. In terms of mechanism, if intestinal flora, metabolism, power, and other angles can be integrated to study, it can be more convincing.

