### Study objective and hypotheses

2.1

This exploratory research project aims to study the effectiveness of QJTCF and light vegetarian therapy for functional constipation and the changes of short-chain fatty acids in feces before and after treatment.

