**Table 3 T3:**
[figure not shown]
The component of Chinese herb powder.

Patients with dietary interventions should follow the above, while patients without dietary interventions will continue their previous dietary habits. The treatment period is 28 days. During the treatment period, record the daily diet and defecation diary. The diet diary will be designed using a semi-quantitative food frequency method, and the defecation diary will collect information about the feeling of defecation, the shape of feces, and the time of each bowel movement. On the 14th day, the patient will be followed up by phone to know the status of the treatment process, and calculate the average number of complete spontaneous bowel movements (CSBMs) per week for the first 14 days, the average score of constipation symptoms and TCM syndrome. After 28 days of treatment, a second follow-up visit will be conducted to understand the condition of constipation (same as the first follow-up visit), and the patient will be required to complete the examination (48 hours gastrointestinal transit Time [GITT], high-resolution anorectal manometry [HRAM], blood routine [BR], liver and kidney function [LKF]). The short-chain fatty acids of the patient 's fresh stool (<30 min) should also be checked and the diary should be retrieved. During the intervention, patients will keep in touch with the researchers. The patient's diet and stool diary will be filled out by the doctor. Keep in touch with each patient in the treatment period through mobile phone software (WeChat), ask the patient to send 3 meals to the doctor's mobile phone, ask the patient about the stool on the day at 7 o’clock every night, and urge patients in the diet intervention group to insist on light vegetarian diet.

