#### Primary outcome

2.11.2

The number of CSBM per week is the primary outcome. It is effective when the number before the intervention subtracted from the number after the intervention is more than or equal to 1.

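### Without a placebo plus usual-diet arm, the trial can estimate only add-on effects of herb and diet, yet the aim is stated as the efficacy of each without qualification

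*Protocol article*

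**What the plan says.** Section 2.2 of the Protocol article allocates patients to "Chinese medicine group (group A), placebo + diet group (group B), Chinese medicine + diet group (group C) at the ratio of 1: 1: 1". Section 2.7 (the text after Table 3) says that "patients without dietary interventions will continue their previous dietary habits", so arm A is herb on usual diet. Every randomised patient therefore receives the herb, the diet or both. Section 2.8 blinds the drug and leaves the diet open.

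On the aim, section 2.1 says the project "aims to study the effectiveness of QJTCF and light vegetarian therapy for functional constipation", and the Discussion says "This RCT aims to clarify the efficacy and safety of LVD and QJTCF on FC by designing rigorous trials". The Introduction notes that rigorous evidence for the two treatments is lacking and presents this trial as the means to verify their effectiveness and safety.

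The primary outcome (section 2.11.2) is complete spontaneous bowel movements (CSBM) per week, with a per-patient classification: "It is effective when the number before the intervention subtracted from the number after the intervention is more than or equal to 1". Section 2.14 plans the test: "Wilcoxon rank sum test or Kruskal–Wallis H test will be used for the number of CSBM per week in primary outcome". It does not name which pairs of arms are to be compared. Section 2.5 says "this study is a small sample exploratory study with a total sample size of 90 people (each treatment group has 30 samples".

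The Discussion lists three limitations: obstacles to following the diet, no metabolites other than short-chain fatty acids (SCFA), and small size. The absent control cell is not among them.

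**The concern.** Herb (yes or no) and diet (yes or no) form a two-by-two layout, and the trial fills three of its four cells. Without the cell that receives neither treatment, neither treatment alone has a concurrent control. The Discussion reports, as a clinical observation, that improvement is maintained in patients who keep to the diet without drugs. That is a stand-alone use of LVD, and the design does not isolate it.

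What is at stake is the conclusion, not the conduct of the trial. If C and A turn out alike, the diet may still work in patients who do not take the herb. If C and B turn out alike, the herb may still work in patients on their usual diet. A report that follows the stated aim could answer those questions wrongly in either direction, or could fall back on before-after change within an arm, which has no comparator.

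**Working it through.** **The plan's own figure.** 3 arms × 30 = 90, which agrees with section 2.5. No effect size, standard deviation or power is given, so there is nothing further to reproduce.

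**What three arms identify.** Let μ0 be the mean change in CSBM per week with neither treatment, h the effect of the herb alone, d the effect of the diet alone, and i their interaction. Then:

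- A = μ0 + h
- B = μ0 + d
- C = μ0 + h + d + i

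There are four unknowns and three arm means (design rank 3 of 4). The pairwise contrasts are:

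- C − B = h + i: herb added to diet, randomised and drug-blinded
- C − A = d + i: diet added to herb, randomised but open for diet
- A − B = h − d: the difference between the two treatments, with both factors changing at once

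None of these gives h, d or i separately. If i = 0, C − B gives h and C − A gives d, but that assumption cannot be tested here. Adding a placebo plus usual-diet arm (mean μ0) raises the rank to 4, and all four quantities become estimable.

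**Example.** Suppose all three arms gain 1.5 CSBM per week. This fits two opposite accounts equally well:

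- Neither treatment works: μ0 = 1.5, h = d = i = 0.
- Each works alone, with nothing gained by combining them: μ0 = 0, h = d = 1.5, i = −1.5. Then A = 1.5, B = 1.5 and C = 1.5 + 1.5 − 1.5 = 1.5.

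**Why within-arm 'effective' rates do not help.** The rule in section 2.11.2 compares a patient only with himself or herself. The article gives no CSBM rate, variance or baseline length, so what follows is illustration on assumptions. Take Poisson counts, a baseline of one or two weeks, and a 14-day average after treatment. The probability that after − before ≥ 1 with no treatment effect and no drift is:

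| True rate per week | One-week baseline | Two-week baseline |
|---|---|---|
| 0.25 | 7% | 6% |
| 0.5 | 17% | 13% |
| 1 | 27% | 22% |
| 1.5 | 32% | 26% |
| 2 | 34% | 29% |

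The range of 6% to 34% is about 2 to 10 of 30 patients (30 × 0.06 = 1.8; 30 × 0.34 = 10.2). With an untreated improvement of 0.5 per week and a one-week baseline, the share at true rates of 1 to 2 per week rises to 44% to 46%. A normal model with assumed standard deviations of 1 to 2.5 gives 16% to 34% with no drift and 31% to 42% with a drift of 0.5. The level depends heavily on the assumptions. In each of these cases, though, some patients are classed 'effective' without a treatment effect.

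**A side point on arm B.** By the ratio in section 2.7 the placebo contains 5/(2 + 3 + 5 + 100) = 5/110 = 4.5% QJTCF powder, so arm B is not strictly free of the herb.

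**The case against.** The best defence is that the article never says stand-alone. Efficacy can properly be studied in an add-on design, and both C vs B and C vs A are randomised comparisons. The Discussion also speaks, with a hedge, of the complementary effect of diet on drugs, which is an add-on question. The study is called exploratory in sections 2.1, 2.3 and 2.5, and verification is left to a future large multicentre trial.

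Much of this stands. A reader might infer that the trial can show nothing about efficacy, and that would be wrong: it gives two randomised add-on comparisons, one of them drug-blinded. The defence does not rescue the aim as worded, however. Nothing limits it to add-on effects, the Introduction presents this trial itself as the verification, and the two contrasts that could support it are not named. Exploratory status excuses a small sample, but a larger sample in the same three arms would not identify the missing quantities.

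A reader might also infer that the plan lets all three arms be declared effective if all improve. The text does not support that. Section 2.11.2 classifies patients, not arms, and section 2.14 specifies only between-group rank tests for CSBM per week. That misreading could arise at reporting, but it is not a planned analysis. Nor does the article claim synergy between diet and herb.

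**Conclusion.** The point holds as a mismatch between the stated aim and the design. The trial estimates QJTCF added to LVD and LVD added to QJTCF. It does not identify the stand-alone effect of either treatment or their interaction, and the limitations do not say so. This follows from the arm definitions alone, needs no numerical assumption, and cannot be repaired by a choice of test. The missing cell is the cause. The per-patient rule matters only because it offers a comparison without a control.

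The 6% to 34% range is illustrative. It rests on Poisson counts, true rates of 0.25 to 2 per week, a one- or two-week baseline and a 14-day follow-up average, none of which the documents fix for this rule. It should not be read as a prediction of how many patients per arm will be falsely classed as 'effective'. The article describes the condition as persistent or recurrent, and gives no figure for change without treatment.

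The trial remains useful. The correction changes what it may conclude, not whether it should be run.

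**What to change.** - In section 2.1, the Introduction and the Discussion, restate the aim as two add-on effects: QJTCF versus placebo in patients on LVD, and LVD versus usual diet in patients on QJTCF, the latter open label.
- In section 2.14, name C vs B and C vs A as the efficacy contrasts for CSBM per week, and say that A vs B only compares the two treatments with each other.
- State that within-arm before-after changes and 'effective' rates are descriptive, including the before-after SCFA changes.
- Add the absent placebo plus usual-diet cell to the limitations, noting that the add-on effects equal stand-alone effects only without interaction and that this cannot be tested here.

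This costs wording only and needs no further patients. The downside is a narrower claim. If stand-alone efficacy is the real question, it needs the fourth arm: 4 × 30 = 120 patients at the present arm size, or 90/4 = 22 to 23 per arm within the present total.
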